## Methods/design

### Overall study design

Women diagnosed with PCOS will be recruited at the Grace Fertility and Reproductive Medicine Centre in Vancouver, Canada. This study follows a factorial design (Fig. 1). Participants will be randomized with a 1:1 allocation into two groups: the first group participating in a comprehensive lifestyle intervention program provided by our clinic (“Graceful Lifestyle Changes” (GLC) program) while the second group will be prescribed letrozole to induce ovulation, with the standard physician counseling (Fig. 2). Within each group, participants will be further randomized with a 1:1 allocation to either receive oral myo-inositol or a placebo. Block randomization will be performed at both stages using a computer-generated random numbers table and the software program REDCap. All clinicians, research scientists and participants involved in the study will be blinded to block sizes and allocation of myo-inositol/placebo. A researcher not involved in the study will be responsible for the randomization procedures. A data monitoring committee will not be necessary given the known safety of the proposed interventions. The SPIRIT 2013 Checklist for trial protocols has been included (see Additional file 1).

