### Lifestyle intervention group (GLC)

The GLC group will have weekly check-ins with physicians and educators for 12 consecutive weeks. A wellness booklet designed and provided by clinicians will outline the main concepts being taught. Each week, subjects will receive detailed comprehensive instructions on how to follow a low-glycemic meal plan, incorporate walking 10,000 steps a day, and induce the relaxation response using cognitive behavioural therapy techniques. The low-glycemic-meal plan requires participants to consume 45% of carbohydrates in their diet and no more than 55 g of glycemic load a day, which is similar to previous low-glycemic diet intervention studies. Lists will be provided outlining foods that are low, medium, or high in their glycemic load. Hence, within their overall meal plan, participants will be advised to eat predominantly low-glycemic foods and to limit high-glycemic foods. They will also be provided with a pedometer to record the number of steps taken each day. These steps can be achieved by any form of exercise that participants can sustain. Lastly, participants will practice relaxation response exercises for 20 min daily on their own, in combination with 6 weeks of mindfulness training provided within the 12-week intervention program.

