### Data collection

Participants will complete a 3-day food diary report during the baseline, 4th, 8th, and 12th weeks. Participants will also receive a phone call from a trained researcher to complete a 24-h diet recall at the end of the 2nd, 6th, and 10th weeks. This recall will assess all food consumed in the previous 24 h. These combined methods will aim to assess overall compliance to the low-glycemic diet, provide researchers with information on the length of time that participants take to comply, evaluate any fluctuations in eating habits and compare these two types of nutritional assessments.

Participants will also record their physical activity during the baseline, 4th, 8th, and 12th weeks based on their pedometer recordings and will record the meditation and relaxation exercises performed daily.

Compliance to the physical activity portion will be measured through daily pedometer readings recorded by the participant. Compliance will be ensured additionally through weekly check-ins/weigh-ins and frequent motivational email reminders.

Psychological well-being (depression, anxiety, stress, and quality of life) will be assessed before and after the 12-week intervention by two validated self-report questionnaires: the Depression Anxiety Stress Scale (DASS) and the Fertility-Related Quality of Life tool (FertiQoL) [27, 28].

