### Outcomes

Ovulation is the primary outcome (categorical “yes” or “no”) and frequency of ovulation (nominal “0”, “1”, “2”, or “3”) during the 12-week (84-day) study. The study length allows observation of three potential ovulatory cycles. The upper limit of a normal ovulatory cycle length is 35 days, hence, to document ovulation using progesterone levels in the expected luteal phase, the study may extend to the end of week 14. Ovulation will be identified by assessing the serum progesterone level on day 22 and, if appropriate, will be repeated 1 week later. A progesterone level greater than 10 nmol/L will be used to confirm ovulation. The secondary outcome is conception (categorical “yes” or “no”). Other outcomes that will be evaluated are miscarriage rates, changes in numerical scores of depression, anxiety, stress, and quality of life based on the DASS and the FertiQoL.

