## Statistical methods

The participants’ biochemical and hormonal profiles, physical attributes (body mass index (BMI), hirsutism), ovulatory response, pregnancy status, scores for depression, anxiety, stress and quality of life will be assessed for statistical normality. Each main effect will be compared by analysis of variance (ANOVA) or its non-parametric equivalents. The primary comparison will be between GLC and letrozole. The observed effects of myo-inositol alone are small in clinical experience and there are no reported interactions between myo-inositol and ovulation-induction medications or lifestyle change in the literature. Hence, our power calculations (see below) have been based on the two main effects acting independently. However, our factorial design will provide an opportunity to explore potential interactions (acknowledging the sample size required would change in the presence of interactions) [30, 31]. Categorical data will be compared by chi-square statistics. Differences in dietary intake and dietary composition over time will be compared by ANOVA or its non-parametric equivalent with time as the repetitive measure. Regression analysis will also be performed to determine the individual impacts of diet, activity, and mindfulness on ovulation. In addition, membership in the four PCOS sub-groups will be further explored as a potential predictor for ovulation rates in regression analysis after adjusting for BMI and age.

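### The component regression claims to determine the individual impacts of diet, activity and mindfulness, but can show only associations with self-selected adherence

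*Protocol article*

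**What the plan says.** The Statistical methods section of the protocol article plans a secondary analysis of the parts of the lifestyle programme: "Regression analysis will also be performed to determine the individual impacts of diet, activity, and mindfulness on ovulation". The next sentence plans a regression on PCOS phenotype, described as exploratory and adjusted for BMI and age. The component sentence has neither qualification.

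Under Lifestyle intervention group (GLC), each woman receives weekly instruction on "how to follow a low-glycemic meal plan, incorporate walking 10,000 steps a day, and induce the relaxation response". The three parts are delivered together to the whole arm.

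Under Overall study design, two things are randomised. First, "Participants will be randomized with a 1:1 allocation into two groups", meaning GLC or letrozole. Then, within each group, "participants will be further randomized with a 1:1 allocation to either receive oral myo-inositol or a placebo".

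The timing is spread over two sections:
- Diet (Data collection): "Participants will complete a 3-day food diary report during the baseline, 4th, 8th, and 12th weeks". A telephone interviewer also helps them "complete a 24-h diet recall at the end of the 2nd, 6th, and 10th weeks".
- Activity (Data collection): "Participants will also record their physical activity during the baseline, 4th, 8th, and 12th weeks". The same section also has compliance measured from daily pedometer readings.
- Relaxation (Data collection): practice is logged daily.
- Outcome (Outcomes): "Ovulation will be identified by assessing the serum progesterone level on day 22", with a repeat one week later if appropriate, over up to three cycles.

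**The concern.** To determine an individual impact is a causal aim, and it needs variation in each component that is unrelated to prognosis. Here the only variation within the GLC arm is how closely each woman follows each part. That is her own choice. It is likely to share causes with ovulation, such as BMI, motivation and general well-being.

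Timing adds a second difficulty. Ovulation can be confirmed from day 22, while diet records continue to week 12. If adherence is summarised over the whole study, part of the predictor for a woman who ovulates early is recorded after her outcome, and may be altered by knowing the result or by pregnancy.

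At stake is how the component results are read. The Background hopes to identify more specifically which factors affect outcomes, so a spurious component effect could be reported as a finding about what makes the programme work.

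**Working it through.** **1. What is identified.** The randomised contrasts are GLC versus letrozole and myo-inositol versus placebo. Diet, steps and relaxation do not differ by design between any two GLC women. No component contrast is randomised, whatever model is fitted.

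**2. Time order.** Suppose cycle day 1 is near study start (an assumption; the article does not tie the two together). The week-2 recall is at about day 14, and the week-4 diary falls in days 22–28.
- For an ovulation confirmed at the first day-22 test, the diet records that clearly precede it are the baseline diary and the week-2 recall. Those of weeks 6 to 12 follow it.
- For a third-cycle ovulation most diet records precede the test.
- Daily step and relaxation logs can be cut at any test date.

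**3. Sample size for the check.** The article gives no figure for this regression, so the GLC arm sizes were used: 91 evaluable, 120 enrolled. The 91 reproduces from the median row of Table 1 (70% v 50%, two-sided 5%, 80% power, unpooled variance):

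n = (1.960 + 0.842)² × (0.70×0.30 + 0.50×0.50) / 0.20² = 7.85 × 0.46 / 0.04 = 90.3, so 91 per group and 182 in total, as stated.

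**4. Simulation.** Ovulation (50%) was regressed on three adherence scores by logistic regression, with every true component effect zero. The quantity reported is the chance that at least one component reaches p<0.05. All strengths below are assumptions; the documents give none.
- *Confounding:* a shared trait U correlates 0.5 with each score (so the scores correlate 0.5² = 0.25 with each other), and logit P(ovulation) = gU with g = 0.5 or 1.0 per SD (odds ratio 1.65 or 2.72).
- *Reverse influence:* g = 0, and each score rises by 0.3 SD in women who ovulate.

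| Setting, n = 91–120 | At least one inert component p<0.05 |
|---|---|
| Neither mechanism | about 11–14% |
| Confounding, log-odds 0.5 to 1.0 | about 28–72% |
| Reverse influence, component correlation 0.25–0.5 | about 25–44% |
| Reverse influence, components uncorrelated | up to about 76% |

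The first row is ordinary multiplicity: three independent tests give 1 − 0.95³ = 14.3%. With weaker confounding (odds ratio 1.5 per SD, component correlation 0.3–0.5) the rate is 20–28%; at odds ratio 2.0 it is 38–51%.

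**5. Pooling the arms.** The article does not say which arm or arms enter the model. With 70% v 50% ovulation, n = 120 per arm, inert components and an assumed 1 SD adherence difference between arms, a false component finding occurs in about 20% of trials without an arm term and about 13% with one.

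**The case against.** The strongest reply is that this is a condensed article, and that the adherence summary, time window, arm and covariates of a secondary regression are what a full protocol or SAP would settle. That stands for those details. A reader might infer that the planned regression does use adherence recorded after the outcome. The article does not say so: it names no window, and the baseline records, the week-2 recall and the daily logs make a properly ordered analysis possible. Post-outcome measurement is a risk, mainly for an early ovulation paired with a whole-study summary.

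A reader might also infer that parts of the programme will be kept or dropped on this result. Nothing says that. The Discussion aims at a comprehensive programme, the Background argues for the combination, and component effects are not among the stated objectives.

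The simulated rates rest on assumed inputs, and the high ones are fragile. The upper end for reverse influence needs uncorrelated components, which sits badly with a bundled programme. If only half the ovulators shift, the rate at n = 91 is about 25% even when uncorrelated. The upper end for confounding needs a trait with an odds ratio of 2.7 per SD.

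What the reply does not remove is the aim itself. No later specification can make a design that randomises none of the components determine their individual impacts.

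**Conclusion.** The point holds as a mismatch between a stated causal aim and a design that supports only association. It should be corrected, but it is confined to a secondary analysis: the randomised comparison of GLC with letrozole and its sample size are untouched. The absence of a named adjustment is a weaker strand, resting on the contrast with the adjacent phenotype regression; the timing problem is conditional on a window that the article leaves open.

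The simulation shows direction and plausible scale, not a prediction for this trial. Both mechanisms push the false-finding rate well above the 11–14% expected from three tests alone, by an amount that depends on confounding strength, on any post-ovulation shift and on the correlation between components.

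**What to change.** 1. Reword the aim in Statistical methods as exploring associations between adherence to each component and ovulation, and reserve causal statements for the randomised comparisons.
2. Fit the model within the GLC arm, per cycle, using only adherence recorded before that cycle's progesterone test.
3. Adjust for baseline BMI, age and phenotype.
4. State that confounding by motivation remains. Baseline adjustment removes only the part of a shared trait that BMI, age and phenotype carry, so step 1 is needed even when steps 2 and 3 are done.

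The cost is small: all the data are already planned, and the article reports that recruitment had not begun. The price is weaker claims about components, somewhat more modelling (repeated cycles per woman), and few diet records before the first-cycle test, so diet will be the least well measured component there.

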In addition to a low-glycemic diet, physical activity, and stress reduction, a diet supplemented with myo-inositol may provide further hormonal homeostasis and improve metabolic functioning [20]. Myo-inositol is one of nine stereoisomers of inositol and sometimes considered a member of the B complex vitamin family, albeit humans can synthesize this isomer from glucose. It acts as a second messenger in insulin signaling pathways. Several studies have shown that insulin resistance with its compensatory hyperinsulinemia play a pivotal role in both the metabolic and ovarian hormone dysfunction observed in PCOS women. There is evidence that women with PCOS and insulin resistance could be deficient in myo-inositol which would impact glucose metabolism. In addition, myo-inositol levels in follicular fluid are lower in PCOS women with hyperinsulinemia compared to healthy women [21, 22]. An earlier study described that higher levels of myo-inositol in follicular fluid correlated with oocyte quality and maturity [23]. When supplemented with myo-inositol, women with PCOS have experienced reduced serum insulin, testosterone, and increased rates of ovulation [24, 25]. Myo-inositol has also been shown to improve oocyte number and quality [26].

We hypothesize that implementing a comprehensive program of lifestyle changes in women with PCOS will help restore ovulation by weight loss, reduce serum androgen levels and increase sensitivity to insulin. A lifestyle change program could also ameliorate hirsutism over time. Such changes should improve overall psychological well-being and quality of life. Finally, we expect that distinct phenotypes of PCOS will respond differently to lifestyle intervention. Such information will allow us to better determine which phenotypes are best served using our comprehensive approach, and to identify more specifically those factors affecting outcomes.

The objectives of this study are: to determine whether the comprehensive lifestyle intervention described is effective in restoring ovulation and compare this to letrozole; to determine whether the addition of myo-inositol improves ovulation rates, insulin resistance, metabolic parameters; and finally to evaluate differences in the responses for each of four main PCOS phenotype sub-groups.

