### Sample size and power calculations

Assuming no interactions between the two main effects as discussed earlier, the target sample size will be 240 participants (120 participants in the GLC group and 120 participants on oral medication). This is based on: a power calculation using a 5% significance level, 80% power comparing two proportions, and current knowledge of the average ovulation rates of lifestyle interventions and letrozole, our primary comparison. We explored a number of combinations of the ovulation rates from letrozole and lifestyle interventions and chose the most conservative estimate to ensure that our sample size was adequate, i.e., 91 in each group. By enrolling 120 participants in each group, we have allowed for a drop-out rate of 32%. Table 1 describes the lowest and highest reported ovulation rates for letrozole and lifestyle interventions, the sample size required in each scenario comparing the two proportions, and the three highest sample sizes required from our calculations, accounting for the length of lifestyle intervention and the start dose of letrozole.

**Table 1 Tab1:** Sample size calculation based on previous literature

Range of reported ovulation rates	Letrozole ovulation rate	Lifestyle ovulation rate	Total sample size needed
Lowest	62%^a^	38%^b^	130
Highest	86%^c^	67%^d^	150
Median	70%	50%	182

^a^Legro et al. [29]

^b^Palomba et al. [36]

^c^Zeinalzadeh et al. [37]

^d^Karimzadeh and Javedani [38]

When calculating the sample size necessary to assess the effect of myo-inositol on ovulation rates, we reviewed the few published studies available acknowledging that these studies all had small sample size. One randomized controlled trial reported an ovulation rate of 70% when myo-inositol was given to women with PCOS versus a 21% ovulation rate in controls [24]. Similarly, another randomized controlled trial reported an ovulation rate of 65% using myo-inositol in PCOS [32]. Using these rates in a comparison of two proportions, a total sample size of 26 is needed, and easily covered by our original calculation above.

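### The only phenotype analysis named estimates how often each PCOS phenotype ovulates, not whether the GLC-versus-letrozole effect differs by phenotype, which is what the Background wants to learn

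*Protocol article*

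**What the plan says.** Three statements in the Background of the protocol article bear on phenotype. The hypothesis is that "we expect that distinct phenotypes of PCOS will respond differently to lifestyle intervention". The intended use follows: "Such information will allow us to better determine which phenotypes are best served using our comprehensive approach". The last listed objective is "finally to evaluate differences in the responses for each of four main PCOS phenotype sub-groups".

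Under Statistical methods, one sentence deals with phenotype: "membership in the four PCOS sub-groups will be further explored as a potential predictor for ovulation rates in regression analysis after adjusting for BMI", to which the text adds age. The sentence does not say whether the regression uses both arms or only GLC, and it names no term or comparison that crosses phenotype with treatment.

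The same section states that "The primary comparison will be between GLC and letrozole". It also says that "our factorial design will provide an opportunity to explore potential interactions". That remark follows a discussion of myo-inositol combined with ovulation-induction drugs or lifestyle change, so it concerns the two randomised factors and not phenotype.

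**The concern.** Asking which phenotypes a programme serves best is a question about treatment effect by phenotype, and in this trial the alternative to GLC is letrozole. A regression of ovulation on phenotype answers another question: which phenotypes ovulate more often. The two answers can point in different directions. A phenotype could be reported as well suited to GLC because it ovulates often whatever it is given, and a phenotype whose outcome depends strongly on the arm could go unnoticed. Readers would probably use such a result to decide whom to offer lifestyle treatment.

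**Working it through.** **1. The plan's own figure.** Sample size and power calculations describes "a power calculation using a 5% significance level, 80% power comparing two proportions", with median rates of 70% (letrozole) and 50% (lifestyle). Taking the test as two-sided, which the text does not state:

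n per group = (1.96 + 0.8416)² × [0.7×0.3 + 0.5×0.5] / (0.7 − 0.5)² = 7.849 × 0.46 / 0.04 = 90.3, so 91 per group and 182 in total.

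This matches the plan and is not in dispute. It supplies the rates and numbers for step 5.

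**2. Prognosis and effect modification are different quantities.** The documents give no rates by phenotype, so these are assumed, with 1:1 allocation:

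| Phenotype | Letrozole | GLC | Average | Letrozole − GLC |
|---|---|---|---|---|
| X | 80% | 40% | (80+40)/2 = 60% | 40 points |
| Y | 60% | 60% | (60+60)/2 = 60% | 0 points |

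The averages are equal, and the treatment effects differ by 40 points.

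**3. Both arms analysed together.** Two further assumed scenarios use 91 per arm and four equally common phenotypes. Expected likelihood-ratio statistics come from logistic models that already contain a treatment term; BMI and age are left out.

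- *A, purely prognostic.* Letrozole rates are 55/65/75/85%, with the same odds ratio in every phenotype, (0.5/0.5)/(0.7/0.3) = 0.43. GLC rates are then 34/44/56/71%. The phenotype main-effect test rejects about 86% of the time and the interaction test 5%.
- *B, purely effect-modifying.* Letrozole 85/75/65/55%, GLC 35/45/55/65%, so every phenotype averages 60%. The main-effect test rejects 5% of the time and the interaction test about 77%.

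Adding treatment as a main effect therefore does not solve the problem; the interaction term does.

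**4. GLC arm only.** The cancellation in step 2 does not arise here, because 40% and 60% would be compared directly. Scenario A then shows the other failure. Ovulation under GLC runs from 34% to 71% across phenotypes although the odds ratio against letrozole is the same in all four. Without the letrozole arm, that gradient cannot be told apart from differential benefit.

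**5. Precision of the right quantity.** The 95% half-width for the treatment difference within one phenotype is 1.96 × √[(0.21 + 0.25)/n], with n per arm in that phenotype:

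- four equal phenotypes, 120 per arm: n = 30, giving 0.243;
- four equal phenotypes, 91 per arm: n = 22.75, giving 0.279;
- a phenotype with a 10% share, 91 per arm: n = 9.1, giving 0.441.

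For one phenotype against the rest, with share f and N per arm, the standard error of the difference in treatment effects is √[0.46/(Nf) + 0.46/(N(1−f))]. With N = 91:

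| Share f | SE | Power for a 20-point difference | Difference giving 80% power |
|---|---|---|---|
| 10% | 0.237 | 13% | 66 points |
| 25% | 0.164 | 23% | 46 points |
| 50% | 0.142 | 29% | 40 points |

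With N = 120, power for 20 points is 16%, 29% and 37%.

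**The case against.** The strongest reply is that the article condenses a fuller plan and fixes less than the concern needs. Naming BMI and age as adjusters does not exclude treatment. The sentence just before concerns diet, activity and mindfulness, which are components of GLC, so the phenotype regression may be meant for the GLC arm. There it would show directly whether ovulation under GLC varies by phenotype, a plain sense of the hypothesis. The objective sentence names neither GLC nor letrozole, and the article elsewhere uses ovulatory response for the outcome itself, so ovulation by phenotype could be said to meet it. The analysis is exploratory, no sample size rests on it, and an interaction test would usually be inconclusive for moderate differences.

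Much of this stands. The analysis population and full covariate list are open, the objective taken alone is general, and power is low. It does not remove the point. The article does name a phenotype analysis and its role, and on either reading that analysis estimates prognosis. The stated use, finding whom the programme serves best, needs the contrast with the alternative treatment. Low power is a reason for intervals and an exploratory label, not for estimating a different quantity.

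**Conclusion.** The point holds as a mismatch between the purpose in the Background and the one phenotype analysis named under Statistical methods. It should be corrected, but it is secondary: the GLC-versus-letrozole comparison and its sample size are untouched.

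A reader might infer three stronger things that the documents do not support:

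- That the planned model omits treatment. The text is silent on this; it does not exclude it.
- That the stated objective cannot be answered at all. The objective sentence is general, and the link to lifestyle treatment comes from the hypothesis and the intended use beside it.
- That the planned analysis would find nothing. This holds only under assumed rates that cancel exactly, with both arms analysed together.

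The 40-point example, the 86%/5% and 5%/77% contrasts and the phenotype shares are all assumptions. They show that the two quantities can diverge, not that they will in this trial.

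**What to change.** Under Statistical methods, specify one logistic model for ovulation (yes/no) in all randomised participants, with GLC/letrozole, myo-inositol/placebo, phenotype, phenotype × GLC/letrozole, BMI and age. Report the interaction test (3 df) and the GLC − letrozole difference in ovulation with its 95% CI within each phenotype. Label all of it exploratory, and state in advance that a non-significant interaction will not be read as equal response across phenotypes.

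If only prognosis by phenotype is intended, narrow the Background statements to say so.

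The cost is analysis wording. Arm, phenotype, BMI, age and ovulation are already part of the plan, and Trial status says that recruitment has not begun, so the change can still be prespecified. The one drawback is the low precision shown above, worse for rarer phenotypes.
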